### Sample Size

The sample size was determined using G*Power version 3.1.9.2, considering the arm volume as the primary outcome. A confidence level of 95%, statistical power of 90%, and a two-sided alpha of 5% were considered in the analysis. An effect size of 0.70 (d) has been chosen to detect differences in the arm volume in patients with BC undergoing chemotherapy; hence, 44 participants will be needed per group. Considering a dropout rate of 20%, 106 patients will be included in the study.

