**Participants:**

One hundred and six women at high risk for breast cancer-related lymphedema aged 18 to 70 years.

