### Randomization

Patients will be randomly allocated (1:1 ratio) in two concealed numerical lists using the software Sealed Envelope™. The software generates different codes for each patient, which then identifies the group linked to the code. The code will be printed and placed in a dark closed envelope, which will be delivered to patients after baseline assessments. A blinded external researcher will perform the process. The allocation will be then reported to the nurse, who will subsequently inform each participant of the assigned group (intervention or control).

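### The enrolment target of 106 covers about 17% dropout, not the stated 20%; at 20% dropout, power is about 89% rather than 90%

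*Protocol article*

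**What the plan says.** The calculation is in the Sample Size section of the protocol article. Arm volume is the primary outcome, and the inputs are "statistical power of 90" percent, "a two-sided alpha of 5% were considered in the analysis", and a standardised effect: "An effect size of 0.70 (d) has been chosen to detect differences in the arm volume". The result is that "44 participants will be needed per group". The dropout allowance follows directly: "Considering a dropout rate of 20%, 106 patients will be included in the study". Allocation is equal (Randomization: "Patients will be randomly allocated (1:1 ratio"), so 106 means 53 per group. The abstract gives the same total under Participants: "One hundred and six women at high risk for breast cancer-related lymphedema". The article does not write out the formula for the dropout allowance and describes no other adjustment or rounding.

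**The concern.** A dropout rate is ordinarily the share of enrolled patients who are lost. To finish with a required number, that number is divided by one minus the rate. Multiplying by one plus the rate always gives too few patients, because the loss applies to the larger enrolled number and not to the number required. The step from 88 to 106 looks like the multiplication.

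If so, the section's statements conflict: 106 enrolled with 20% lost does not leave the 44 per group that the same section says are needed for 90% power. Readers and ethics committees rely on this sentence to judge whether the trial can answer its question, so it should be right even where the shortfall is modest.

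**Working it through.** **Inputs.** All come from the protocol article: d = 0.70, two-sided alpha 0.05, power 0.90, 44 per group, 20% dropout and total 106 (Sample Size); 1:1 allocation (Randomization). The effect is standardised, so no standard deviation is needed. The section names the software but not the test; a two-sample t-test is assumed.

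**Step 1: reproduce 44 per group.** Power is taken from the noncentral t distribution with n₁ + n₂ − 2 degrees of freedom and noncentrality d × √(n₁n₂/(n₁ + n₂)).

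- For 44 and 44: noncentrality 0.70 × √22 = 3.283, 86 degrees of freedom, critical value 1.988, power 90.09%.
- For 43 and 43: power 89.4%.

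So 44 is the smallest group size that reaches 90%. The plan's figure is reproduced exactly, and it has almost no slack.

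**Step 2: reproduce 106.**

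| Rule | Per group | Total |
|---|---|---|
| Multiply: n × (1 + 0.20) | 44 × 1.20 = 52.8 → 53 | 88 × 1.20 = 105.6 → 106 |
| Divide: n / (1 − 0.20) | 44 / 0.80 = 55 | 88 / 0.80 = 110 |

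The stated total matches multiplication exactly. Division gives 110, which no rounding turns into 106.

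**Step 3: what 106 leaves after 20% dropout.** 106 × 0.80 = 84.8 in total, or 53 × 0.80 = 42.4 per group, against the 44 required.

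**Step 4: power with what is left, at d = 0.70.**

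| Completers | Power | d detectable with 90% power |
|---|---|---|
| 44 + 44 | 90.1% | 0.699 |
| 42 + 43 | 89.0% | 0.712 |
| 42 + 42 | 88.7% | 0.716 |

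If each patient independently has a 20% chance of dropping out of groups of 53, power averaged over the possible numbers of completers is 88.8%. With a normal approximation in place of the t distribution, 42 per group gives 89.4% and 42.4 per group gives 89.7%, still below 90%.

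**Step 5: the dropout that 106 does cover.** 1 − 88/106 = 18/106 = 17.0%.

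**The case against.** Four points can be made for the plan.

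1. *The formula is not printed.* That 106 came from multiplying by 1.20 is a reconstruction. This is true, but the match is exact, and the conclusion does not depend on how 106 was obtained: 80% of 106 is 84.8 by any route.

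2. *Multiplying is defensible if 20% is read as extra patients relative to completers.* That reading corresponds to 0.20/1.20 = 16.7% of those enrolled. The section speaks of a dropout rate, whose ordinary meaning is the share of enrolled patients lost, and gives no sign of the other reading.

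3. *The planned analysis is not a t-test on completers.* The abstract names linear mixed models, and Statistical Analyses describes a repeated-measures model over four time points under intention to treat. Patients lost after the first post-intervention assessment can still contribute, and including baseline can change precision. As an illustration, suppose d is scaled by the cross-sectional standard deviation and the contrast is change from baseline, with variance factor 2(1 − ρ). Then 42 per group does as well as 44 once 2(1 − ρ) ≤ 42/44, that is, once ρ is at least about 0.52; a lower ρ than that does worse. The document gives neither ρ nor the scale of d, so the power of the actual analysis may lie above or below 90%. This part of the objection stands: the 17% limit applies to the calculation as stated and is not a proven limit for the mixed model. It does not repair the dropout sum, which is set against 44 per group with no reference to partial data.

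4. *The effect is trivial.* It is small, about 1.1 to 1.4 percentage points of power. That limits the weight of the point, not its truth.

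**Conclusion.** The point holds. The 44 per group is right; the allowance added to it is not. With 20% of enrolled patients lost, 106 leaves about 42 per group and 88.7% to 89.0% power at d = 0.70. The total is four patients short of the 110 that the stated assumptions require, and it covers 17.0% dropout. The power figures assume a two-sample t-test on completers, which reproduces the plan's own 44, and dropout expressed as a share of those enrolled.

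This is an arithmetic error of minor consequence. It does not make the trial seriously underpowered, but the sample-size statement is wrong as written and should be corrected.

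**What to change.** Keep 106 and correct the sentence in Sample Size in one of two ways:

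- state that 106 patients allow for about 17% dropout while keeping 44 per group and 90% power for d = 0.70; or
- state that 106 patients with 20% dropout leave about 42 per group, giving about 89% power for d = 0.70.

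Either change is one sentence, needs no extra patients and leaves the total in the abstract as it is. The cost is a slightly less favourable stated dropout allowance or power. The alternative is to keep both 20% and 90% and enrol 110 (55 per group), which means four more patients and a corrected total in the abstract.

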### Randomization

Patients will be randomly allocated (1:1 ratio) in two concealed numerical lists using the software Sealed Envelope™. The software generates different codes for each patient, which then identifies the group linked to the code. The code will be printed and placed in a dark closed envelope, which will be delivered to patients after baseline assessments. A blinded external researcher will perform the process. The allocation will be then reported to the nurse, who will subsequently inform each participant of the assigned group (intervention or control).

### Study Assessments

**Figure 3** outlines the schedule for study outcome assessments. Assessments will be scheduled upfront, and patients will be regularly reminded *via* phone or email. Outcomes will be measured at four-time points: [t0] at baseline (up to 7 days before chemotherapy); [t1] after intervention (up to 5 days after the intervention ended); [t2] at three months of follow-up; and [t3] at six months of follow-up. Assessments will be made by an experienced researcher blinded to the allocation of patients.

**Figure 3 f3:**
[figure not shown]
Study design. *Breast cancer at high risk for breast cancer-related lymphedema (BCRL) has been established as having had: [a] total or partial mastectomy with axillary node dissection; [2] sentinel node biopsy with positive axillary web syndrome; or [3] sentinel node biopsy along with a body mass index between 30.0 and 39.9; F, frequency; I, intensity; T, type; T, time.

### Data Management

Two researchers will manage data using predesigned data collection forms in Excel version 2016 (Microsoft Corporation, Redmond, WA, USA). Data will be regularly revised to ensure data quality. Patients will be identified by codes to ensure anonymity, and only the authors involved in the trial will have access to patients’ full identification details.

### Statistical Analyses

Analyses will be performed by a statistician blinded to the allocation of patients. Intention-to-treat and per-protocol approaches will be used. Normality assumption will be tested using the Shapiro-Wilk test. If the normality assumption is met, data will be presented using means and standard deviations. Otherwise, median and interquartile ranges will be reported. To assess the effect of the intervention, a multivariate linear regression model with repeated measurements will be adjusted. The model will include arm volume, quality of life, physical performance, and handgrip strength as response variables. Group (intervention, control), time (t0, t1, t2, t3), and the group×time interaction will be included as explanatory variables, adjusted for co-variables if required. The intervention’s effect will be also described by computing the effect size and 95% confidence limits. The following qualitative descriptors will be used: trivial <0.20, small 0.20-0.50, moderate 0.50-0.80, and large >0.80 (62). Significance will be set at p<0.05. Statistical analyses will be performed with STATA 15.1.

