**Main Outcome Measures:**

The primary outcome will be arms volume measured with an optoelectric device (perometer NT1000). Secondary outcomes will be quality of life, handgrip strength, and physical performance. Primary and secondary outcomes will be measured at baseline, just after the intervention, and 3 and 6 months after. Statistical analysis will be performed following intention-to-treat and per-protocol approaches. The treatment effect will be calculated using linear mixed models.

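### No arm-volume test is designated primary, and the 90% power belongs to a simpler comparison than the planned group×time model

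*Protocol article*

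**What the plan says.** Three places in the protocol article bear on the primary analysis.

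- **Statistical Analyses.** A multivariate linear regression for repeated measurements is planned: "The model will include arm volume, quality of life, physical performance, and handgrip strength as response variables". Its explanatory terms are group, time (t0 to t3) and their interaction, "adjusted for co-variables if required". Effect sizes with 95% limits will also be given. Significance is p<0.05, with no outcome, visit or term attached.
- **Abstract, Main Outcome Measures.** Arm volume is the primary outcome; quality of life, grip strength and physical performance are secondary. The method is different: "The treatment effect will be calculated using linear mixed models".
- **Sample Size.** The calculation was made "considering the arm volume as the primary outcome". It takes 90% power, a two-sided test at 5% and a standardised difference of 0.70, and arrives at this: "hence, 44 participants will be needed per group". It gives no visit, no difference in millilitres, no SD and no within-patient correlation.

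Study Assessments lists four time points and ranks none. The Discussion puts all four outcomes under the main objective.

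**The concern.** The article names a single primary outcome but does not say which estimate or test of it decides the trial. The analysis section puts primary and secondary outcomes in one response set and supplies a group×time term with three degrees of freedom per outcome. The abstract points to another model. The sample size assumes a comparison of two means, with one degree of freedom.

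Two things are at stake. First, a claim of effect could rest on any outcome, visit or term that falls below 0.05 and still comply with the written plan. Second, the 90% power describes a test that the analysis section does not identify as the one to be run.

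**Working it through.** **Inputs from the article:** d = 0.70, two-sided alpha 0.05, power 90%, 44 per group, four visits. **Assumptions, because the article gives no correlation:** compound symmetry over visits with within-patient correlation ρ of 0.3, 0.5 or 0.7; complete data.

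**1. The stated figure.** For a two-sample t-test, the noncentrality is λ = d²·n/2 = 0.49 × 44/2 = 10.78 on 1 and 86 df. Power is 90.1%; 43 per group gives 89.4%. So 44 per group reproduces exactly as a two-sided, 1-df comparison of arm volume.

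**2. The group×time test for arm volume alone.** This has 3 numerator df (three changes from t0) and 88 − 2 − 3 + 1 = 84 denominator df.

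- *Noncentrality held at 10.78:* power is 77.4%, and 60 per group would be needed for 90%.
- *d = 0.70 on the raw SD, at t1 only or at all three post-baseline visits:* λ = 10.78 × 0.75/(1 − ρ).

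| ρ | λ | Power, 3-df test |
|---|---|---|
| 0.3 | 11.55 | 80.5% |
| 0.5 | 16.17 | 92.5% |
| 0.7 | 26.95 | 99.4% |

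For an effect that wanes (0.70, 0.35, 0), power is 76.6%, 89.9% and 99.0% at the same ρ. The 3-df test therefore lies below or above 90% according to a correlation and a scale for d that the article does not fix.

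**3. False positives if any visit counts.** Three contrasts of arm volume against t0 share the baseline. Under compound symmetry each has variance 2(1 − ρ) and each pair has covariance (1 − ρ), so any two correlate 0.5 whatever ρ is. Testing each at 0.05 and accepting any one gives about 12.5% (simulation). Independence would give 1 − 0.95³ = 14.3%.

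**4. Handling of t0.** With a free group difference at t0, the group×time coefficient at a visit is a difference in change from baseline. With d on the cross-sectional SD, the standardised effect is d/√(2(1 − ρ)) for change and d/√(1 − ρ²) with t0 as covariate; constraining the t0 means to be equal gives essentially the same gain.

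| ρ | Effect, change | Power | Effect, adjusted | Power |
|---|---|---|---|---|
| 0.3 | 0.592 | 78.3% | 0.734 | 92.5% |
| 0.5 | 0.700 | 90.1% | 0.808 | 96.3% |
| 0.7 | 0.904 | 98.7% | 0.980 | 99.5% |

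The variance ratio, adjusted to change, is (1 + ρ)/2.

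**The case against.** The strongest reply is that the wording is loose rather than wrong. Quality of life is two questionnaires and grip is measured in both hands, so there is no literal four-element response. Read with the abstract, the sentence may simply list the outcomes to which the same repeated-measures model is applied. That reading is possible, but it still leaves no visit, contrast or term designated for arm volume, and the two descriptions of the model still need reconciling.

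Several stronger readings are tempting and are not supported:

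- **That arm volume has no test of its own.** A multivariate linear model yields separate coefficients and tests for each response, and no joint test is specified. What is missing is the designation of one as primary.
- **That the trial is underpowered, or could succeed through grip strength alone.** This needs a joint test that the article does not state. Even then, a four-outcome test at one visit, with an effect on arm volume only, has 72% power with uncorrelated outcomes but 92% at a between-outcome correlation of 0.5.
- **That the type I error for arm volume is not 5%.** A single 3-df interaction test holds 5%. The 12.5% needs an any-visit rule, which the article neither states nor excludes.
- **That women with any missing outcome must be excluded.** This depends on how the model is fitted. Mixed models use the available visits, and missing-data handling commonly sits in the analysis plan.
- **That a covariate for the high-risk route is required.** Covariate lists are ordinary analysis-plan content in a condensed article.

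On t0, it is fair to say that a change contrast is unbiased under randomisation and that the loss is small at high correlation. The point there is efficiency, not validity.

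**Conclusion.** The point holds in limited form. The article describes the primary analysis in two ways, sizes the trial for a third and simpler comparison, and designates no arm-volume test as primary. This is a conflict within the stated text, not a detail left to an analysis plan.

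The 90% cannot be carried over to the group×time analysis, but it is not shown to be too high or too low. The 3-df arm-volume test has about 77% power with noncentrality fixed at 10.78. With d on the raw SD, under compound symmetry, it has about 80% at ρ = 0.3 and about 90% or more from ρ of about 0.5. The 12.5% error rate is conditional on counting any of three visits. The loss from a change-score contrast runs from about 14 percentage points at ρ = 0.3 to under 1 at ρ = 0.7, and assumes that d refers to the cross-sectional SD.

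**What to change.** Make the abstract and the Statistical Analyses section agree, as follows:

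1. Fit one linear mixed model per outcome, using all available visits.
2. Name one group contrast in arm volume at one visit as the primary test, two-sided at 5%. Label the other visits and outcomes secondary.
3. Constrain the t0 means to be equal between groups, or use t0 as a covariate.
4. In Sample Size, say that d = 0.70 and the 90% power refer to that contrast and on which scale (cross-sectional, change or baseline-adjusted). If 0.70 is the standardised effect of the named contrast, 44 per group fits as it stands.

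This changes wording only and needs no new data. The cost is that arm volume at the visits not chosen becomes secondary. The choice should be made before any outcome data are seen by group.

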## Introduction

Breast cancer is the leading cause of cancer mortality among women worldwide (1–3). While early detection and better treatment strategies have improved overall survival (4, 5), patients often develop adverse effects such as fatigue, pain, sensory loss, impairments in shoulder range of motion and muscle strength, axillary web syndrome, and lymphedema (6–10). These effects ultimately impair survivors’ quality of life and physical performance (11–14).

Among the adverse effects, lymphedema deserves attention because of its chronic nature (15). One-third of breast cancer survivors develop breast cancer-related arm lymphedema (BCRL), 80% of them closely after treatments (16–18). BCRL is an excess accumulation of protein-rich fluid that would otherwise drain *via* the lymphatic system, leading to regional swelling in one or both arms after breast cancer (19, 20). BCRL has multifactorial causes, influenced by treatment strategies and the patient’s ability to form collateral lymphatic pathways post-injury (20, 21). Major risk factors for BCRL are obesity (body mass index ≥30 kg/m^2^), extensive breast and axillary lymph node surgery, radiotherapy in lymph node basin, and taxane chemotherapy (10, 14, 20, 22). Clinically, BCRL is characterized by increased arm volume associated with pain, heaviness, tightness, and a decreased range of motion, thus impacting the quality of life (23, 24).

The treatment for BCRL focuses on volume control through physiotherapy and compression garments (25–27), which represents a high economic burden for patients and the health care system (28). Identifying strategies to prevent BCRL in individuals at high risk, and to improve quality of life of patients is necessary (27).

Historically, there has been objection to promoting physical exercise or weight lifting to breast cancer survivors (29). Nevertheless, this is currently regarded as safe (30). Indeed, there has been an emerging interest in physical exercise (aerobic and resistance) as a safe and effective complementary intervention to prevent or diminish the adverse effects related to breast cancer treatments (31–33).

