### Sociodemographic and Clinical Data

Demographic data will include age, sex, and educational level. Anthropometric data will include weight, height, and body mass index. Clinical data will include disease stage, scheduled treatment, medical history, and current medication. Clinical data will be extracted from the patients’ electronic medical files by one study coordinator not blinded to patient allocation.

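### The repeated-measures model lets the groups differ at t0, although t0 precedes disclosure of the allocation; a common baseline would sharpen the treatment contrast at almost no cost

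*Protocol article*

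**What the plan says.** The model is set out in the Statistical Analyses section of the protocol article: "Group (intervention, control), time (t0, t1, t2, t3), and the group×time interaction will be included as explanatory variables, adjusted for co-variables if required". The sentence before it lists the responses: "The model will include arm volume, quality of life, physical performance, and handgrip strength as response variables". The abstract gives the method in one line: "The treatment effect will be calculated using linear mixed models". Nothing in the article enters the baseline value as a covariate or sets the t0 means of the two groups equal.

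On timing, the Randomization section says of the allocation envelope: "which will be delivered to patients after baseline assessments". The t0 measurement therefore comes before anyone can act on the allocation.

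The Sample Size section plans 44 participants per group for an effect size d of 0.70, two-sided alpha of 5% and 90% power. It does not say whether d is scaled by the SD of a single visit or the SD of change. It gives no correlation between visits.

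On who does the analysis, the Statistical Analyses section says: "Analyses will be performed by a statistician blinded to the allocation of patients".

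**The concern.** In a randomised trial, a group difference at a visit before allocation is known can only be chance. A model with group, four time levels including t0, and their full interaction still estimates that difference as a free parameter. Each group×time term is then the difference between groups in raw change from t0. Subtracting the whole baseline value, instead of the part that predicts follow-up, adds noise.

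What is at stake is precision for arm volume and for each secondary outcome given the same model. Bias is not at stake. There is also a smaller matter: covariates enter on a condition that the article does not define, so whether to adjust, and for what, could be settled after data are seen.

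**Working it through.** **Inputs from the protocol article.** d = 0.70, two-sided alpha 5%, power 90%, 44 per group (Sample Size); visits t0 to t3 (Study Assessments); model terms (Statistical Analyses). **Assumed:** rho, the correlation between t0 and a follow-up visit, over a range; equal variance at each visit; complete data.

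**Step 1: reproduce the plan's figure.** For a plain comparison of two means, the noncentrality is d × √(n/2) = 0.70 × √22 = 3.283. The noncentral t distribution with 86 degrees of freedom gives power of 90.1% at 44 per group; 43 per group gives 89.4%. The stated 44 is confirmed. It takes no credit for baseline information.

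**Step 2: variance per patient, in units of the single-visit variance.**
- Raw change, Y − Y₀ (the group×time term as written): 2(1 − rho).
- Baseline-adjusted, Y − rho·Y₀ (baseline as covariate or common t0 mean): 1 − rho².
- Ratio of adjusted to raw change: (1 − rho²) / [2(1 − rho)] = (1 + rho)/2, which is below 1 for every rho below 1.

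| Assumed rho | Raw change | Adjusted | Ratio | Variance saved |
|---|---|---|---|---|
| 0.5 | 1.00 | 0.75 | 0.75 | 25% |
| 0.7 | 0.60 | 0.51 | 0.85 | 15% |
| 0.8 | 0.40 | 0.36 | 0.90 | 10% |
| 0.9 | 0.20 | 0.19 | 0.95 | 5% |

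**Step 3: check on the full four-visit model.** Generalised least squares with 44 per group, comparing a free with a common t0 mean, gives ratios of 0.75, 0.90 and 0.95 at rho 0.5, 0.8 and 0.9 when all visits are equally correlated. These match Step 2. If correlation decays with time (first-order autoregressive, rho between adjacent visits), the ratios at t3 are 0.56, 0.76 and 0.86, so the loss at the last visit is larger.

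**Step 4: what this means for power at 44 per group (noncentral t).** The answer depends on the scale of d.

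*If d = 0.70 is on the single-visit SD*, the effective effect size is 0.70/√(variance factor):

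| Assumed rho | Raw change | Adjusted |
|---|---|---|
| 0.3 | 78.3% | 92.6% |
| 0.4 | 84.2% | 94.3% |
| 0.5 | 90.1% | 96.3% |
| 0.6 | 95.3% | 98.2% |
| 0.7 | 98.7% | 99.5% |

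*If d = 0.70 is on the SD of change*, the raw change contrast has 90.1% power whatever rho is. Adjustment divides d by √[(1 + rho)/2] and gives 96.3%, 94.1%, 92.8% and 91.5% at rho 0.5, 0.7, 0.8 and 0.9.

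**The case against.** The strongest reply is that nothing in the model is wrong. Group, time and their interaction with t0 as a response is a standard, unbiased analysis of a randomised trial, and 44 per group does not rely on any gain from baseline. That stands, and it makes this an improvement to the plan, not a correction of an error.

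The size may also be small for the primary outcome. If arm volume in the same woman is highly correlated over time, the saving is about 5% at rho 0.9. The test-retest coefficient of 0.99 under Main Outcome describes the instrument and does not give rho over the months from t0 to follow-up. It does mean that measurement error is unlikely to be what pulls rho down. The same model serves quality of life, walking distance and grip strength, where rho could be lower and the saving larger.

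A reader might infer that the trial is underpowered, or that its stated power depends on a hidden correlation. The article does not support this. A shortfall for the change contrast arises only if d is on the single-visit SD and rho is also below 0.5, and the article states neither. It also does not say that the primary contrast is change from t0; a between-group difference at a follow-up visit is the comparison that reproduces 44.

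A reader might also infer that covariates will be picked to suit the result. The article does not say so. The analyst is blinded to allocation, which limits choice by treatment result although it does not fix the choice. A covariate list may properly sit in a statistical analysis plan that is not shown, so its absence here is not a fault. What remains is an undefined condition in the wording.

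**Conclusion.** The point holds as an efficiency improvement. The model spends information on a t0 group difference that is zero in expectation by design. Its group×time terms are therefore less precise than baseline-adjusted ones for any rho below 1. The variance saving is 25% at rho 0.5 and falls to 5% at rho 0.9. It is larger at t3 if correlation decays with time. These sizes rest on assumed correlations and on equal variance across visits; the direction holds for any rho below 1.

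The analysis as written is not invalid and the stated power is not refuted. The conditional covariate wording is a secondary point about clarity.

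**What to change.** In Statistical Analyses, state that the t0 mean of each outcome is common to both groups, and that group×time terms are estimated at t1, t2 and t3 only. Equivalently, enter the baseline value of each outcome as a covariate and model t1 to t3 as the responses. The change needs no new data and no change to the sample size. It costs about one degree of freedom if baseline is used as a covariate.

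As a wording change, replace the open condition on covariates with a decision, recorded before unblinding, on which covariates (if any) enter the primary model. The choice of set is the sponsor's. The Introduction already names candidates ("Major risk factors for BCRL are obesity (body mass index ≥30 kg/m^2^), extensive breast and axillary lymph node surgery"), and the Sociodemographic and Clinical Data section lists what is recorded, including body mass index. Stating that there will be no further covariates would also settle the matter.
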